### Statistical methods

The final analysis will be done on an intent-to-treat group. The median and 95% Confidence intervals (CIs) of OS and PFS will be estimated using the Kaplan–Meier method. Overall survival will be measured from the date of treatment to the date of death or the last follow-up. Progression-free survival will be measured from the date of treatment to the date of first progression or death or the last follow-up.

ORR will be based on the proportion of patients with a best overall response of confirmed CR or PR. ORR 95% will be estimated using the exact binomial method based on the F-distribution.

EORTC QLQ-C30 (version 3.0) questionnaire will be used to evaluate the quality of life. All scales range in score from 0 to 100. The mean scores will be calculated at baseline and every 2 months after the treatment. The mean ± SD, maximum, minimum, and median values will be used to describe the measurement before and after the treatment.

Mini-Mental State Exam (MMSE, score range 0 to 30) will be used to evaluate the cognitive function. Any score of 24 or more (out of 30) indicates normal cognition. Below this, scores can indicate severe (≤ 9 points), moderate (10–18 points), or mild (19–23 points) cognitive impairment.

The mean ± SD, maximum, minimum, and median values will be used to describe the measurement before and after the treatment.

CTCAE 5.0 will be used to assess the toxicity. The number of events, number of subjects, and the incidence rate will be used to describe the measurement.

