**Methods/design:**

HSCK-010 is an open-label, single-arm phase II trial (NCT04547621) which includes newly diagnosed GBM patients who underwent gross total resection. Patients will receive the combination of 30 Gy/5fx HSRT, and 20 Gy/10fx IMRT adjuvant therapy with concurrent temozolomide and adjuvant chemotherapy. The primary endpoint is overall survival (OS). Secondary outcomes include progression-free survival (PFS) rate, objective-response rate (ORR), quality of life (Qol) before and after the treatment, cognitive function before and after the treatment, and rate of treatment-related adverse events (AE). The combination of HSRT and IMRT with temozolomide can benefit the patients after surgery with good survival, acceptable toxicity, and reduced treatment time.

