### Evaluation, neurological, and quality of life

The assessment will be done every two months, which will include the medical history, vital signs, physical examination, KPS, blood pressure, EKG, MRI (T1 Gad enhanced, T2 FLAIR), blood routine, blood biochemistry, urine routine, stool routine, quality of life score (QLQ-C30 3.0) and cognitive evaluation (MMSE). The measure of response will be by the RANO criteria. An overview of the study assessments and procedures is presented in Table 1.

**Table 1 Tab1:** Data collection schedule

Follow-up							
	Inclusion	Surgery	RT	M2	M4	M6	Mx^a^
Consent	✓						
Medical History	✓						
Physical examinations and vital signs	✓			✓	✓	✓	✓
Blood routine, Hepatic and Renal Function	✓	✓	✓	✓	✓	✓	✓
Pregnancy Test (Childbearing Age Women)	✓						
Dosimetric MRI + CT Scan			✓				
MRI (T1 enhanced, T2 FLAIR)		✓		✓	✓	✓	✓
KPS Score	✓	✓	✓	✓	✓	✓	✓
QLQ-C30 questionnaire	✓	✓	✓	✓	✓	✓	✓
MMSE questionnaire	✓	✓	✓	✓	✓	✓	✓
Toxicity Evaluation (CTCAE 5.0)	✓	✓	✓	✓	✓	✓	✓

^a^The follow-up will be done every two months till death or the patient withdrawal from the study

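### PFS is censored at the last follow-up, as OS is, not at the last tumour assessment, so PFS can be overstated when contact outlasts imaging

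*Protocol article*

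**What the plan says.** Statistical methods defines the two endpoints in parallel. For OS: "Overall survival will be measured from the date of treatment to the date of death or the last follow-up". For PFS: "Progression-free survival will be measured from the date of treatment to the date of first progression or death or the last follow-up". Without an event, both therefore end at the last follow-up. The same section gives the estimator: "The median and 95% Confidence intervals (CIs) of OS and PFS will be estimated using the Kaplan–Meier method". PFS is a secondary outcome.

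Evaluation, neurological, and quality of life sets the schedule: "The assessment will be done every two months, which will include the medical history", followed by a list that contains MRI. It adds: "The measure of response will be by the RANO criteria". Table 1 ticks MRI in each follow-up column (M2, M4, M6 and Mx), and its footnote says: "The follow-up will be done every two months till death or the patient withdrawal from the study". No separate survival-only contact is described.

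**The concern.** Vital status can be learned from any contact. Progression under a RANO-based scheme normally needs a scan. A PFS time is therefore known to be event-free only up to the last adequate tumour assessment. Take a patient whose last MRI is at month 6 and who is seen without a scan until month 12. Under the written rule that patient stays in the PFS risk set as progression-free for six months in which nobody looked. A progression missed in that time is either never counted or is dated at death. Both errors lengthen PFS.

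The dates can separate in this trial. Each visit has many components, so it can go ahead with the MRI missed. Withdrawal criteria allow patients to discontinue for toxicity, non-compliance or on request, without progression. If vital status is still sought for such patients, as an intent-to-treat OS analysis would want, contact outlasts imaging.

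The consequence is modest but real. Project duration and expected outcomes expects PFS and OS similar to those reported for standard chemoradiation, and links a supportive result to a phase III trial. With a single arm, no concurrent control shares the bias.

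**Working it through.** **The plan's own figure.** The article gives no number for PFS. Its sample size is for OS: two-sided one-sample log-rank test, alpha 0.05, power 80%, control median 14 months, HR 0.58, 12 months' accrual and 24 months' further follow-up. With exponential survival and the exact-variance formula, N = 44.08, rounded up to 45 (power 0.808 at n = 45). Allowing for 10% loss, 45/0.90 = 50. Both figures reproduce, and neither depends on the PFS sentence.

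**Assumptions for PFS (none is in the documents).** Exponential time to progression, median 7 months; exponential survival after progression, median 9 months; 10%, 20% or 30% of patients stop MRI at a uniformly distributed time in months 0-12, unrelated to their disease; contact then continues for 0, 2, 6 or 12 months.

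**From the documents.** MRI every 2 months, uniform accrual over 12 months, 24 months' further follow-up, and death as a PFS event.

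**Check of the reference value.** With complete scanning, 12-month PFS is 0.5^(12/7) = 0.305. A true median of 7 months is observed at the next scan, month 8.

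**Simulation.** 300,000 patients per scenario, Kaplan-Meier estimate of 12-month PFS. True means complete scanning. Deaths during contact count as events under both rules.

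| Stop MRI | Contact after last MRI | True | Censor at last follow-up | Difference (points) | Censor at last MRI |
|---|---|---|---|---|---|
| 10% | 2 months | 0.304 | 0.311 | +0.7 | 0.304 |
| 10% | 6 months | 0.307 | 0.323 | +1.6 | 0.304 |
| 10% | 12 months | 0.303 | 0.326 | +2.3 | 0.302 |
| 20% | 2 months | 0.305 | 0.318 | +1.3 | 0.304 |
| 20% | 6 months | 0.306 | 0.340 | +3.4 | 0.301 |
| 20% | 12 months | 0.304 | 0.351 | +4.7 | 0.301 |
| 30% | 2 months | 0.304 | 0.326 | +2.2 | 0.302 |
| 30% | 6 months | 0.303 | 0.357 | +5.4 | 0.295 |
| 30% | 12 months | 0.306 | 0.375 | +6.9 | 0.301 |

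With no gap between last contact and last MRI, both rules return the true value (0.304 to 0.306). Censoring at the last MRI is within 0.8 of a point of the truth in every row, and never above it.

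**Median.** In these large samples the median is 8.0 months under both rules, except 8.2 under the written rule in the last row. Part of this stability comes from the scan grid, because the median stays on the month-8 visit. In simulated trials of 50 patients with the same stopping pattern, the average estimated median under the written rule reaches 8.8 months in the worst case.

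**If stopping is informative.** Suppose patients miss the very scan that would have shown progression (post-progression median 8 months, contact until death or study end). True 12-month PFS is 30.5%. For 10/20/30% stopping, the written rule gives 34.4/38.3/42.1%. Censoring at the last MRI, with events after two missed scans also censored, gives 33.2/36.3/39.6%. The share of the bias that remains is 2.7/3.9 = 69%, 5.8/7.8 = 74% and 9.1/11.6 = 78%.

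**The case against.** The strongest reply is that the article uses follow-up for a specific visit, and every such visit includes an MRI. On that reading the last follow-up is an MRI visit, and OS and PFS share a censoring date because they share visits. This stands as far as it goes. A reader might infer that PFS in this trial is biased upward, or that survival follow-up means any contact. The documents support neither: no survival-only contact is described, no missed-scan rate is given, and with complete scanning the bias is zero. Nor do they say that progression can be recognised only on imaging, since each assessment also includes a physical examination and KPS. What remains is that the sentence gives the wrong date whenever scan and contact part company.

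A second reply is that censoring conventions belong in the SAP. That would answer a gap, but here the article states a rule, and states it in the same terms as for OS.

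Third, larger effects on the median, about 1 month, can be produced. They come from trials of 50 patients with many stopping MRI and a long stretch of unscanned contact, so they are upper-end figures and not an expectation. Counting deaths as PFS events limits the bias further.

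Fourth, censoring at the last MRI is not a cure. If deterioration drives the missed scans, most of the bias remains, as the last calculation shows. Discarding deaths after two missed scans is a debatable convention. Both points are accepted and shape the fix.

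**Conclusion.** The point holds in a conditional form and is minor. The PFS sentence names the wrong censoring date. This does no harm if every scan is done, and acts upward if contact outlasts imaging. On the assumed rates, with random stopping, 12-month PFS is overstated by roughly 0.5 to 7 percentage points and 6-month PFS by about 0.6 to 3.5 points, with little effect on the median in most cases. These figures depend on an assumed 7-month median, an assumed 10-30% of patients stopping MRI and assumed gaps of 2-12 months. PFS is secondary, is described without a test or threshold, and has no formal part in a decision rule. The OS analysis and the sample size of 45 (50 with losses) are untouched.

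**What to change.** Change the PFS sentence so that patients without progression or death are censored at the date of their last evaluable MRI/RANO assessment. Keep last follow-up as the censoring date for OS only. In the main analysis, keep deaths as PFS events. Use the rule that censors a progression or death after two or more missed assessments at the last assessment before the gap only as a sensitivity analysis.

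The cost is one sentence of wording, slightly less PFS follow-up time and possibly a slightly shorter reported PFS. If scanning is complete, nothing changes. The new rule reduces the bias but does not remove it when patients stop scanning because they are deteriorating, or when deaths long after the last scan are counted. Reporting how many patients had contact beyond their last MRI, and for how long, would let readers judge what is left.

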### Secondary outcomes

To estimate the following factors:The progression-free survival (PFS) rate.The objective-response rate (ORR).The quality of life (Qol) before and after the treatment.The cognitive function before and after the treatment.The rate of treatment-related adverse events (AE).

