## Study design

### Inclusion criteria

18–70 years of age;Karnofsky performance status (KPS) ≥ 60 within 14 days prior to registration;Histopathologically proved diagnosis glioblastoma multiforme;Underwent surgery, gross total resection, or subtotal resection;Estimated survival of at least 3 months;Hgb > 90/gL; absolute neutrophil count (ANC) > 1.5 × 109/L, platelets > 80 × 109/L; Creatinine < 1.5 times the upper limit of laboratory normal value; Bilirubin < 2 times the upper limit of laboratory normal value; serum glutamate pyruvate transaminase (SGPT) or serum glutamate oxaloacetate transaminase (SGOT) < 3 times the upper limit of laboratory normal value;Signed informed consent form;Agreed to participate in the follow-up.

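### The objective response rate is not restricted to patients with measurable residual tumour, although the trial enrols after gross total resection, so read as written it is diluted by the resection mix

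*Protocol article*

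**What the plan says.** ORR is one of five items under Secondary outcomes. Statistical methods defines it: "ORR will be based on the proportion of patients with a best overall response of confirmed CR or PR". The interval is fixed there too: "ORR 95% will be estimated using the exact binomial method based on the F-distribution". The same section opens with the only analysis set named in the article: "The final analysis will be done on an intent-to-treat group". The section on evaluation adds: "The measure of response will be by the RANO criteria".

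On who is enrolled, the article gives two descriptions. The abstract speaks of "newly diagnosed GBM patients who underwent gross total resection". The inclusion criteria read "Underwent surgery, gross total resection, or subtotal resection". Neither the inclusion nor the exclusion list requires measurable disease after surgery.

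Under Treatments, the HSRT target is drawn from the contrast-enhanced T1 scan together with the margins of the surgical cavity. A patient with no residual enhancement therefore still has a target, is treated, and belongs to the intent-to-treat group.

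**The concern.** A response rate needs something that can respond. A patient who starts radiotherapy with no measurable enhancing tumour has no lesion whose shrinkage can be recorded as a partial response. If such patients sit in the denominator, the ORR falls as the share of complete resections rises, whatever the radiotherapy does. Two cohorts with the same response rate among measurable patients would report different ORRs because their surgeons left different amounts of tumour behind.

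The disagreement between the abstract and the inclusion criteria bears directly on this, because extent of resection largely determines how many patients have measurable disease. The trial has one arm, so no concurrent control shares the distortion, and its results are meant to inform a phase III trial.

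**Working it through.** **Inputs from the article.** The numerator is confirmed CR or PR. The denominator is given as patients, with intent-to-treat the only named set. Planned enrolment is 50: 45 subjects with 10% loss to follow-up, and 45 / (1 − 0.10) = 50, which agrees. The article states no target, precision or expected value for ORR, so it has no ORR figure to reproduce.

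**Inputs that are assumptions.** Neither of these is in the article:
- g, the share of patients with no measurable enhancing disease before radiotherapy;
- r, the true response rate among patients who do have measurable disease.

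**Formula.** If patients without measurable disease count as non-responders,

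ORR over all patients = (1 − g) × r.

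The ratio to the rate among measurable patients is (1 − g) r / r = 1 − g. The relative dilution thus depends only on g.

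**Illustration with r = 30%.**
- g = 40%: 0.60 × 0.30 = 18%.
- g = 60%: 0.40 × 0.30 = 12%.

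**Other assumed values, N = 50, exact (Clopper–Pearson) 95% intervals.**

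| g | r | Measurable patients | Responders | ORR over all 50 (95% CI) | ORR in measurable patients (95% CI) |
|---|---|---|---|---|---|
| 30% | 20% | 35 | 7 | 14% (5.8 to 26.7) | 20% (8.4 to 36.9) |
| 50% | 20% | 25 | 5 | 10% (3.3 to 21.8) | 20% (6.8 to 40.7) |
| 70% | 20% | 15 | 3 | 6% (1.3 to 16.5) | 20% (4.3 to 48.1) |
| 30% | 40% | 35 | 14 | 28% (16.2 to 42.5) | 40% (23.9 to 57.9) |
| 50% | 40% | 25 | 10 | 20% (10.0 to 33.7) | 40% (21.1 to 61.3) |
| 70% | 40% | 15 | 6 | 12% (4.5 to 24.3) | 40% (16.3 to 67.7) |

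Two things follow. The all-patient rate moves with g while the rate among measurable patients stays where it was set. The all-patient interval is narrower, but it is an interval for the diluted quantity: with g = 50% and r = 40% it runs from 10.0% to 33.7% and excludes 40%.

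**The case against.** **The denominator is inferred.** The ORR sentence says patients, not all patients, and the intent-to-treat sentence is general. A response-evaluable subset is often set out in an analysis plan or full protocol, neither of which is shown. This stands as a limit on confidence. It does not remove the point: the article does define ORR and its interval, names one analysis set, and attaches them to a population in which a patient may have nothing to measure. Following the definition as printed gives the diluted rate.

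**A reader might infer that the ORR could equally be inflated.** If tumour-free scans were coded as CR, the rate would be (1 − g) r + g; with r = 30% that is 0.18 + 0.40 = 58% at g = 40% and 0.12 + 0.60 = 72% at g = 60%. No section states such a coding. Response is assigned to the RANO criteria, whose handling of a tumour-free baseline cannot be checked from the article. Inflation is a possibility to close off, not a finding.

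**A reader might also infer from the abstract that nobody can respond and that ORR is meaningless.** That is too absolute. The inclusion criteria admit subtotal resection. The article does not define gross total resection or say that imaging confirms it, and Treatments contours the IMRT target from enhancement and FLAIR or T2 abnormality on the post-operative MRI, so residual abnormality is expected in some patients. What g measures is absence of measurable enhancement, which need not equal the share labelled gross total.

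**The sizes are hypothetical.** This is correct: g and r are assumptions, and the table shows a range, not a prediction.

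**Conclusion.** The point holds in a limited form. As written, ORR is not confined to patients with measurable residual disease, although the inclusion criteria admit gross total resection and the abstract mentions nothing else. On that reading the reported rate is the measurable-patient rate multiplied by 1 − g: for example 18% or 12% in place of 30% when g is 40% or 60%. This rests on two things: reading the denominator as the intent-to-treat group, and counting patients without measurable disease as non-responders. Both g and r are assumed.

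Separately, the abstract and the inclusion criteria contradict each other on extent of resection. That conflict is on the face of the text and needs no assumption.

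The consequence is confined to one descriptive secondary outcome with no target or power attached. The primary OS analysis and the sample size are unaffected. Confidence is moderate. The change should be made, but it is not critical to the trial.

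**What to change.** - In Statistical methods, compute ORR and its exact 95% CI only in patients with measurable residual enhancing disease on the post-operative, pre-radiotherapy MRI, and report that number as the denominator.
- Report patients without measurable disease as not evaluable for response, with their number. They stay in the OS and PFS analyses. This also rules out counting a scan that was tumour-free at baseline as a CR.
- Reconcile the abstract with the inclusion criteria on extent of resection. If only gross-total-resection patients are enrolled, drop ORR or limit it to those with measurable residual enhancement on MRI.

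The cost is a sentence or two in Statistical methods and a correction wherever the statements on extent of resection differ. No new scan is needed, because Treatments already requires an MRI for planning and uses the post-operative scan; measurability at baseline has to be recorded from it. The statistical price is precision: with g = 50% and r = 40%, the interval goes from 10.0–33.7% on 50 patients to 21.1–61.3% on 25.

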### Evaluation, neurological, and quality of life

The assessment will be done every two months, which will include the medical history, vital signs, physical examination, KPS, blood pressure, EKG, MRI (T1 Gad enhanced, T2 FLAIR), blood routine, blood biochemistry, urine routine, stool routine, quality of life score (QLQ-C30 3.0) and cognitive evaluation (MMSE). The measure of response will be by the RANO criteria. An overview of the study assessments and procedures is presented in Table 1.

**Table 1 Tab1:** Data collection schedule

Follow-up							
	Inclusion	Surgery	RT	M2	M4	M6	Mx^a^
Consent	✓						
Medical History	✓						
Physical examinations and vital signs	✓			✓	✓	✓	✓
Blood routine, Hepatic and Renal Function	✓	✓	✓	✓	✓	✓	✓
Pregnancy Test (Childbearing Age Women)	✓						
Dosimetric MRI + CT Scan			✓				
MRI (T1 enhanced, T2 FLAIR)		✓		✓	✓	✓	✓
KPS Score	✓	✓	✓	✓	✓	✓	✓
QLQ-C30 questionnaire	✓	✓	✓	✓	✓	✓	✓
MMSE questionnaire	✓	✓	✓	✓	✓	✓	✓
Toxicity Evaluation (CTCAE 5.0)	✓	✓	✓	✓	✓	✓	✓

^a^The follow-up will be done every two months till death or the patient withdrawal from the study

### Data management

All data will be recorded in the CRF and submitted to the data center. The study investigators will collect and restore pseudonymized electronically in compliance with local regulations. Pseudonymized data will be accessible to all investigators and full data access will be given to related supervising authorities.

### Quality assurance and safety considerations

The treatment-related adverse events will be defined according to the CTCAE 5.0. The AE will be monitored and recorded by laboratory tests, clinical examinations, and MRI. Acute neurotoxicity will be defined as any treatment-related neurologic adverse events occurring within 4 weeks after the last day of radiotherapy. Late neurotoxicity will be classified as those that happen 3 months after radiotherapy, and the rest (4 weeks to 3 months) defined as early delayed neurotoxicity. Pseudoprogression and radiation necrosis (RN) are common events in brain tumor patients who underwent radiotherapy [8]. MR Spectroscopy (MRS) or L-[methyl-(11)C]-methionine (MET) positron emission tomography (PET) will be considered to distinguish the events [9, 10].

The Institutional Review Board (IRB) will receive the report of all recorded adverse events exceeding CTCAE 5.0 Grade 2 for evaluation. Any serious adverse events will be reported to the IRB within 24 h.

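### The protocol says CTCAE 5.0 defines treatment-related events but otherwise uses it only for severity, so the listed safety rate rests on open-label attribution and needs an all-cause rate beside it

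*Protocol article*

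**What the plan says.** The secondary outcomes include "The rate of treatment-related adverse events (AE"), and the abstract lists the same outcome. No other adverse-event outcome is listed.

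The section Quality assurance and safety considerations then states: "The treatment-related adverse events will be defined according to the CTCAE 5.0". It applies the same restriction to neurologic events: "Acute neurotoxicity will be defined as any treatment-related neurologic adverse events occurring within 4 weeks after the last day of radiotherapy". The late and early delayed classes in the next sentence refer back to this definition and differ from it only in timing.

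That section calls pseudoprogression and radiation necrosis common after brain radiotherapy. It foresees MR spectroscopy or methionine PET to separate them, in permissive terms: "positron emission tomography (PET) will be considered to distinguish the events". On oversight, the review board "will receive the report of all recorded adverse events exceeding CTCAE 5.0 Grade 2 for evaluation".

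Under Statistical methods the wording is different: "CTCAE 5.0 will be used to assess the toxicity", followed by "The number of events, number of subjects, and the incidence rate will be used to describe the measurement". Neither sentence mentions relatedness.

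**The concern.** Whether an event is treatment-related decides whether it enters the listed safety outcome and the neurotoxicity classes. The article gives the definition of that term to an instrument that it uses elsewhere only for severity. Read literally, the sentence leaves the cause of an event undefined, and the decision falls to whoever judges attribution. In an open-label trial that person knows the treatment. In a single-arm trial there is no control rate in which attribution error would also appear.

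This matters more here than in many trials. New neurologic signs after cranial radiotherapy can come from the treatment or from the tumour, and the article itself foresees extra imaging to tell such events apart. The abstract speaks of acceptable toxicity, and the trial is meant to support a phase III trial. A reader of the results will therefore want a toxicity figure that does not turn on individual judgements of cause.

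**Working it through.** **Step 1. How the article uses CTCAE and relatedness.**

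| Place in the protocol article | Content | Limited to treatment-related events? |
|---|---|---|
| Abstract; Secondary outcomes | Listed adverse-event outcome | Yes |
| Quality assurance and safety, first sentence | CTCAE 5.0 said to define the events | Yes |
| Same section, neurotoxicity classes | Acute class, with late and early delayed referring back | Yes |
| Same section, reporting to the review board | Events above grade 2 | No |
| Statistical methods | Events, subjects and incidence rate for toxicity | No filter stated |
| Table 1 | CTCAE toxicity evaluation in every column | No |
| Exclusion criteria | Bleeding of CTCAE grade 3 or more | Not applicable: severity only |

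Where a CTCAE level is actually applied (the bleeding exclusion and the reporting threshold), it is a severity grade. Only the first sentence of the safety section asks CTCAE to settle relatedness. The listed outcome is restricted to related events while the analysis text is not, so the article supports two readings of which rate will be published.

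**Step 2. Is there a stated figure to reproduce?** No. The article gives no expected adverse-event rate, threshold or precision target.

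**Step 3. What one judgement is worth.** The planned sample size is 50 (Sample size and power justification). If a patient's only event in a class is reclassified, the per-patient rate for that class moves by 1/50 = 2 percentage points.

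**Step 4. Direction of error.** This step uses assumed inputs only. It shows what sign the error can take and is not evidence about this trial. Let

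- T = share of patients with a treatment-caused neurologic event
- U = share with tumour-caused decline, taken as separate patients
- m = share of T blamed on tumour
- f = share of U blamed on treatment

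Reported rate = T(1 - m) + U × f, so error = -T × m + U × f.

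With T = 20% and U = 50%:

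- m = 50%, f = 0: 20% × 0.50 + 0 = 10%, error -10 points
- m = 25%, f = 10%: 20% × 0.75 + 50% × 0.10 = 15% + 5% = 20%, error 0
- m = 0, f = 25%: 20% + 50% × 0.25 = 32.5%, error +12.5 points

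Over T 10-30%, U 20-50%, m 0-50% and f 0-25%:

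- lowest error: -30% × 0.50 = -15 points
- highest error: 50% × 0.25 = +12.5 points

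The sign depends on m and f, and the article says nothing that fixes either.

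**The case against.** A reader might infer that the toxicity rate is understated and that the regimen will look safer than it is. The documents do not support that. Understatement needs a treatment-caused event to be wrongly blamed on tumour. Decline truly due to tumour is correctly left out of a treatment-related rate, and tumour decline blamed on treatment inflates it. Progressive disease is listed as a ground for discontinuation, and Table 1 ends follow-up at death or withdrawal, so a treatment effect misread as progression could also cut short later toxicity collection. The discontinuation wording is permissive, however, so this is a risk and does not establish a net bias.

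Other points on this side also have weight:

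- Events are recorded and graded at every scheduled visit, and the review board sees those above grade 2 whatever their cause. Nothing prevents all-cause reporting. This is oversight and data capture, however, and not the listed outcome.
- Imaging to separate treatment effect from tumour is foreseen. It is optional, so it reduces the dependence on judgement without removing it.
- Lack of blinding and of a control arm belongs to the declared design. A causality procedure, and any intervals on descriptive rates, may sit in the full protocol or analysis plan, which are not shown. Their absence from the article is not part of this point.
- Making neurotoxicity itself all-cause would mislabel it. The Background says nearly all patients recur, the late class starts at 3 months, and follow-up runs until death or withdrawal, so such a count would largely track progression.

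These arguments narrow the point. They do not rescue the sentence that assigns relatedness to CTCAE, nor do they settle which rate will be reported.

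**Conclusion.** The point holds in a limited form. The article states wrongly that CTCAE 5.0 defines which events are treatment-related, restricts its listed adverse-event outcome and neurotoxicity classes to those events, and then describes the toxicity summary without that restriction. The listed rate therefore depends on unblinded attribution and can err in either direction. Its size cannot be derived from the documents: the 2 points per patient assume a denominator of 50, and the range from -15 to +12.5 points rests wholly on assumed inputs.

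The outcome is secondary and descriptive, with no decision rule. No significance level, power, sample size or primary analysis changes. It is a worthwhile, inexpensive correction and does not threaten the trial's main conclusion.

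**What to change.** 1. Replace the sentence on the definition of treatment-related events with one saying that CTCAE 5.0 supplies adverse-event terms and severity grades, and that relatedness is judged separately.
2. Report all-cause adverse events and all-cause neurologic events from the first IMRT day, by worst grade per patient. Show the neurologic events in the same acute, early delayed and late windows.
3. Show the treatment-related subset beside them, and keep the label neurotoxicity for the related neurologic events only.
4. Word the toxicity summary under Statistical methods so that it names both sets.

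The cost is a few sentences and one more table column. Adverse events are already recorded and CTCAE evaluation is already in every column of Table 1, so no new assessments are needed. The drawback is that the all-cause figures will be higher because they include tumour-related events. The neurologic ones, especially in the late window, must be read with progression in mind, which is why the related subset stays alongside.
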